## Abstract

**Background:**

Vitreoretinal surgery in anticoagulated patients is a challenging situation for vitreoretinal surgeons, who have to choose between being faced with the systemic thromboembolic risks that the interruption of anticoagulation involves, or the intra- and postoperative haemorrhagic risks associated with maintenance of this therapy. So far, no trial has compared, in a prospective and randomized manner, perioperative complications and the visual results associated with continuation or interruption of oral anticoagulant therapy before pars plana vitrectomy (PPV) under retrobulbar anaesthesia. The main objective of this trial is to compare haemostasis-related perioperative complications of PPV in patients maintaining anticoagulant therapy before surgery compared to patients with an interruption in this therapy before surgery.

**Methods:**

Ninety-six patients will be randomly assigned to either the control group, in whom oral anticoagulant therapy will be interrupted and substituted with subcutaneous heparin according to local clinical practice, or the intervention group in whom oral anticoagulant therapy will not be interrupted before surgery. Patients will be stratified according to the oral anticoagulant they were taking (direct or indirect anticoagulation). They will be followed up for 12 weeks, and the primary outcome, and haemorrhagic complications until 15 days after surgery, will be evaluated.

**Discussion:**

This trial will provide novel information on the possibility of continuing anticoagulant therapy during PPV. The benefits expected from the change in the current surgical management paradigm for anticoagulated patients would be a decreased risk in the incidence of perioperative thromboembolic events and the possibility of performing surgery without delay and without the need for patients to change their usual anticoagulation protocol to the more complex and less safe substitutive therapy.

**Trial registration:**

Clinical Trials Register EudraCT, 2018–000753-45. Registered on 11 November 2018.

## Background

The administration of anticoagulant drugs to reduce thromboembolic events is a widespread clinical practice, especially among patients of advanced age [1, 2]. Currently, vitamin K antagonists (acenocumarol) or new direct-acting oral anticoagulants (dabigatran, rivaroxaban, apixaban and edoxaban) are being used. Atrial fibrillation is the most frequent indication, but these drugs are also employed in patients with artificial heart valves, ischaemic cardiopathy, deep venous thrombosis, hypercoagulability states and peripheral vasculopathies. The use of these drugs is constantly expanding, and this fact, together with an ageing population, is expected to produce a notable increase in the number of anticoagulated patients over the coming years.

The indication for pars plana vitrectomy (PPV) is being expanded and is likely to continue in the coming years. PPV in patients undergoing anticoagulation represents a challenge for retinal specialists who must carefully evaluate possible trade-offs between the systemic risks associated with interrupting anticoagulant therapy and the intra- and postoperative risks of performing PPV in these cases. Moreover, interruption of anticoagulant therapy and instauration of substitutive therapy is cumbersome for patients and makes it necessary to postpone surgery for a number of days, a situation that can be inconvenient in urgent PPV indications such as retinal detachment.

Most of the studies performed to date to evaluate the risks of anticoagulant therapy during intraocular surgery have been conducted in patients undergoing cataract surgery [3, 4]. There is currently no consensus with regard to the need or otherwise to interrupt oral anticoagulant therapy before vitreoretinal surgery. Most of the authors that have evaluated this issue have done so in a retrospective manner and agree that continuation of anticoagulant therapy before PPV does not pose a significant risk for these patients [5–10].

So far, no trial has compared the perioperative complications and visual results associated with continuation or interruption of oral anticoagulant therapy before PPV under retrobulbar anaesthesia in a prospective and randomised manner. There is only one study that has evaluated this issue in a prospective but nonrandomised manner, but the authors included a small number of patients, did not standardise the management of anticoagulant agents in the perioperative period and did not record all haemorrhagic complications [11]. Moreover, there is only one study that has evaluated haemorrhagic intraoperative complications associated with PPV in patients under treatment with novel anticoagulant therapy [10].

In order to overcome the shortage of works on this topic, we have designed a randomised clinical trial aimed at comparing haemostasis-related perioperative complications of PPV in patients maintaining anticoagulant therapy before surgery compared to patients who have interruption of this therapy before PPV. Additionally, both the incidence of systemic thromboembolic events after PPV and the changes in visual results after PPV will be compared between the groups.

## Methods and design

A randomised clinical trial with two parallel groups will be conducted at the Ophthalmology Department of the Complejo Hospitalario de Navarra in Spain. Clinical management of the patients will be performed according to local current clinical practice except in the experimental group where oral anticoagulant therapy will not be interrupted before surgery. Patients will be stratified according to the oral anticoagulant they are taking (direct or indirect anticoagulation).

### Primary objective

Our main objective is to compare haemostasis-related perioperative complications of PPV in patients maintaining oral anticoagulant therapy before surgery compared to patients with interruption of this therapy before PPV.

### Secondary objectives

Our secondary objectives are to compare changes in the visual results 3 months after PPV in patients who maintain anticoagulant therapy compared to those with interruption of this therapy before surgery and to compare the incidence of systemic thromboembolic events after PPV in those patients who maintain anticoagulant therapy compared to those with interruption of this therapy before surgery.

### Hypothesis

We hypothesise that anticoagulant therapy maintenance before PPV is not associated with a significant increase in perioperative complications compared to those cases in which this therapy is interrupted before surgery, and that the postoperative visual results are not inferior in those cases in which anticoagulant therapy is maintained compared to those cases in which such therapy is interrupted before surgery.

### Participants, recruitment methods and procedures

Patients with a possible clinical indication for PPV identified by any ophthalmologist in the reference area are referred to be evaluated by the vitreoretinal surgeons of the Ophthalmology Department in the Complejo Hospitalario de Navarra, who will confirm the surgical indication, in addition to assessing the medical status and checking the current treatments in each case. The surgeon in charge will invite all subjects receiving oral anticoagulant therapy with a clinical indication for PPV to participate in the study. The purposes, methods, objectives and possible risks associated with the study will be suitably explained to them. A patient information sheet and an informed consent form will be subsequently provided. A specific consent form for the surgery will also be provided to participants. The schedule of enrolment, interventions and assessments is summarized in Figs. 1 and 2. A screening visit will be scheduled for patients who decide to participate in the study. In that visit, the inclusion and exclusion criteria will be assessed (Table 1), and patients will be informed of the group to which they will be assigned, together with the date of their operation. A description of the surgical procedure will also be provided during the screening visit. They will also be scheduled to attend an anaesthesia consultation. If the anaesthetist considers that there is a circumstance that contraindicates the interruption of anticoagulant treatment, the patient will be excluded from the trial. After PPV, they will be followed up in order to assess complications, adverse effects and visual acuity for 3 months.

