### Study randomisation

Upon completion of the screening assessment, participants who satisfy all the inclusion criteria and none of the exclusion criteria will be randomly assigned to the intervention and control groups in a 1:1 allocation ratio. Randomisation will be stratified by oral anticoagulation type: direct anticoagulation, which includes dabigatran, rivaroxaban, apixaban or edoxaban, and indirect anticoagulation, which includes acenocumarol. Randomisation assignment will be computer generated using the ‘randomizr’ library of the R statistical program R 3.4.0, with a complete randomising method based on permutations that guarantees balanced groups. The allocation sequence will be generated by the Methodology Unit of Navarrabiomed. Randomisation will be requested to the Clinical Trials Platform (CTP) of Navarrabiomed by the investigator responsible for patient recruitment. In return, CTP will send to this investigator an answer form by email that includes a randomisation number and the assigned treatment for this patient. Then, the investigator responsible for patient recruitment will give the information about treatment allocation to the anaesthetist, who will inform the patient. Throughout the study, the randomisation will be conducted by the CTP and the randomisation list will be kept by the CTP team for the duration of the study. Randomisation will be conducted without any influence of the investigators. The surgeons in charge, who will measure the outcomes, will be blinded. The data analyst will also be blinded, whereas participants and the rest of the investigators will not be blinded. Unblinding will not be allowed under any circumstance.

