### Study arms

In the control group (representing the standard of care), anticoagulant therapy will be interrupted before surgery and patients will receive substitutive treatment with subcutaneous enoxaparin in accordance with the currently employed protocol in the hospital.

To establish substitution therapy, the thrombotic risk of patients is evaluated, taking into account their clinical characteristics. Their renal function is also evaluated by measuring the glomerular filtration rate. In patients undergoing treatment with acenocumarol, if the thrombotic risk is low, they will be treated with enoxaparin 40 mg/24 h; if the thrombotic risk is high and the glomerular filtration rate is less than 30 ml/min, they will be treated with enoxaparin 40 mg/24 h; if the thrombotic risk is high and the glomerular filtration rate is greater than 30 ml/min, they will be treated with enoxaparin 40 mg/12 h. In patients undergoing treatment with the new direct action oral anticoagulants, if the glomerular filtration rate is less than 50 ml/min or if the thrombotic risk is high, the treatment is replaced 5 days before with enoxaparin 40 mg/24 h. If the glomerular filtration rate is greater than 50 ml/min and the thrombotic risk is low, anticoagulant treatment is suspended without the need for substitution treatment.

For the intervention group oral anticoagulant therapy will not be interrupted. Patients will continue their regular oral anticoagulant therapy before and after surgery.

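### As written, an anaesthetist who has been told the allocation can exclude patients, apparently after randomisation, for a reason that affects treatment only in the interruption arm

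*Protocol article*

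**What the plan says.** Two sections of the protocol article bear on the order of events.

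Under Participants, recruitment methods and procedures, the criteria in Table 1 are assessed at the screening visit, where "patients will be informed of the group to which they will be assigned, together with the date of their operation". The text continues: "They will also be scheduled to attend an anaesthesia consultation". It then states that if "the anaesthetist considers that there is a circumstance that contraindicates the interruption of anticoagulant treatment, the patient will be excluded from the trial".

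Under Study randomisation: "Upon completion of the screening assessment, participants who satisfy all the inclusion criteria and none of the exclusion criteria will be randomly assigned". The recruiting investigator receives the assignment from the Clinical Trials Platform (CTP) and "will give the information about treatment allocation to the anaesthetist, who will inform the patient". The surgeons who measure outcomes and the data analyst are blinded, "whereas participants and the rest of the investigators will not be blinded".

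Under Study arms, the control condition is that "anticoagulant therapy will be interrupted before surgery and patients will receive substitutive treatment with subcutaneous enoxaparin". For the other arm: "For the intervention group oral anticoagulant therapy will not be interrupted".

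**The concern.** Eligibility should be settled before anyone who decides on it can know the arm. Here the last eligibility decision appears to come after allocation and belongs to a person who has been given the allocation. The ground for exclusion is that interruption would be unsafe. In a patient assigned to continue treatment, that ground has no practical consequence, so an anaesthetist who knows the arm has little reason to invoke it there. In a patient assigned to interruption it decides whether the patient stays in the trial.

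If the rule were used mainly in the control arm, the arms would no longer be the groups that randomisation formed. The thromboembolic comparison, a secondary objective and endpoint, is the most exposed, because the reason for removal concerns the hazard of stopping anticoagulation. The primary haemorrhage comparison is affected only if those removed also have a different haemorrhage risk. The article presents the prospective, randomised design as the trial's main strength.

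**Working it through.** **1. Order of events.**

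- Participants section: Table 1 criteria checked and group disclosed at screening; anaesthesia consultation scheduled; possible exclusion by the anaesthetist.
- Study randomisation section: screening completed; randomisation; allocation sent to the investigator; investigator tells the anaesthetist; anaesthetist tells the patient.

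The accounts differ on who tells the patient and when. Neither places the anaesthetist's check before allocation, and the anaesthetist is not among the blinded roles.

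**2. The plan's own sample size.** Inputs from Sample size: 96% complication-free in both arms, margin 10 points, 80% power, 95% confidence (sidedness not stated).

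n per arm = (z_α + z_β)² × 2 × 0.96 × 0.04 / 0.10²

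- One-sided 5%: (1.645 + 0.842)² × 0.0768 / 0.01 = 47.5, so 48. This matches the plan.
- One-sided 2.5%: (1.960 + 0.842)² × 0.0768 / 0.01 = 60.3, so 61. This does not match.

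The rest uses one-sided 5%.

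**3. Power if only controls are lost.** The document gives no exclusion rate. Assume 5–10% of 48, that is 2.4 to 4.8, or 2 to 5 patients.

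Power = Φ(0.10/SE − 1.645), with SE = √(0.0384/n_C + 0.0384/48)

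- n_C = 48: SE 0.0400, power 80.4%
- n_C = 46: SE 0.0404, power 79.6%
- n_C = 43: SE 0.0411, power 78.4%

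**4. How finely the verdict is balanced.** The article names no interval method, so a one-sided 95% Newcombe bound is assumed:

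upper limit = (p_T − p_C) + √[(u_T − p_T)² + (p_C − l_C)²]

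Here T is continuation, C is interruption, and u and l are Wilson limits with z = 1.645. With 48 per arm:

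- 2 vs 2 events: 0 + √(0.0767² + 0.0278²) = 8.2%, pass
- 3 vs 3 events: 0 + √(0.0839² + 0.0373²) = 9.2%, pass
- 3 vs 2 events: 0.0208 + √(0.0839² + 0.0278²) = 10.9%, fail

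Losing one control event can therefore change the verdict, as in the step from 3 vs 3 to 3 vs 2.

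**5. How often it would change.** Overall risk is 4% in both arms and m of 48 controls are removed. If those removed have r times the risk of the others, and f = m/48, the others' risk is 0.04 / (1 − f + f·r). Each trial is evaluated with and without the m controls, with the control denominator reduced to 48 − m, summing over all binomial outcomes.

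| m | r | Events expected among those removed | Remaining control risk | Pass becomes fail |
|---|---|---|---|---|
| 2 | 1 | 2 × 0.04 = 0.08 | 4.0% | 0.7% |
| 5 | 1 | 5 × 0.04 = 0.20 | 4.0% | 1.9% |
| 2 | 3 | 2 × 0.111 = 0.22 | 3.7% | 2.1% |
| 5 | 3 | 5 × 0.099 = 0.50 | 3.3% | 5.1% |

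At equal risk, about 0.5% of trials change the other way, from fail to pass. At r = 3 the spurious difference is 4.0 − 3.7 = 0.3 points (m = 2) or 4.0 − 3.3 = 0.7 points (m = 5), against continuation.

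**The case against.** Much of the case on the other side stands.

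- **The rule names no arm.** Applied identically in both arms it would only reduce numbers. Differential use is an inference about behaviour. What the text lacks is a safeguard: the person applying the rule knows the arm.
- **High thrombotic risk is not the trigger.** A reader might infer that high-risk patients would be dropped from control and kept in the continuation arm. Study arms contradicts this: it sets out how high-risk control patients are handled, for both types of anticoagulant. Exclusion needs some further circumstance, which the article does not define, so neither the number nor the prognosis of those affected can be read from it.
- **Table 1 is not silent.** Exclusion criterion 4 covers medical situations that could interfere with participation or adherence, and arguably includes this one. What is missing is the explicit criterion and the anaesthetist's part in judging it.
- **The sequence is not certain.** The two sections conflict on disclosure, and the timetable and schedule figures are not available here. If the consultation is in fact completed before randomisation, the problem disappears. The text does not say so.
- **An unseen analysis plan may specify analysis as randomised.** That would help only if outcomes were still collected. The article says such patients leave the trial.
- **Direction.** If those removed from control bleed more, continuation looks worse, which works against a false claim of non-inferiority.

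One might also quote the chance that a pass becomes a fail when one control event is lost, which is 11.2% at 4% risk with 48 kept in each arm. That figure assumes a control event is always removed. Removing 2 to 5 controls at 4% removes only 0.08 to 0.20 expected events, so it does not measure the likely effect.

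**Conclusion.** The point holds as a gap in protection. The text allows an exclusion that is unblinded, apparently comes after allocation, and matters for treatment in one arm only. It does not show that the randomised comparison is broken, and a reader should not infer that.

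The size is unknown. On the assumption of 2 to 5 removals from control only, the non-inferiority verdict would turn from pass to fail in about 1–2% of trials at equal haemorrhage risk, and in about 2–5% if those removed had three times the risk (also an assumption). Power would fall by at most about 2 points. The thromboembolic comparison carries the main exposure, and the document gives no figure from which to size it. These results rest on a 4% risk in both arms, a one-sided 5% level and a Newcombe bound. Confidence in the exact order of events is moderate, given the conflict between the two sections. The change is worth making because it is cheap and because selection after randomisation cannot be reliably repaired in the analysis.

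**What to change.** 1. Reconcile Participants, recruitment methods and procedures with Study randomisation on when, and by whom, the patient learns the group.
2. Complete and record the anaesthetist's eligibility check for every candidate before randomisation is requested from the CTP. The anaesthetist can still receive the allocation afterwards, as is needed to verify before surgery that the assigned procedure was followed.
3. Name the anaesthetist's judgement of a contraindication to interruption explicitly among the exclusion criteria in Table 1.
4. Keep anyone already randomised in follow-up and in the analysis, in the assigned arm. Recruitment is under way, so such patients may exist.

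The cost is a short amendment and a small reordering of existing visits. No procedure is added, the clinical judgement itself is unchanged, and the sample size stays at 48 per arm.

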**Fig. 1 Fig1:**
[figure not shown]
Study timetable and assessments. OAT oral anticoagulant therapy, PPV pars plana vitrectomy

**Fig. 2 Fig2:**
[figure not shown]
Schedule of enrolment, interventions and assessments

**Table 1 Tab1:** Inclusion and exclusion criteria

Inclusion criteria	Exclusion criteria
1. Adults over 18 years old of both sexes 2. Clinical indication for PPV alone or associated with facoemulsification or scleral buckling 3. Under treatment with any of the following oral anticoagulants: acenocumarol, dabigatran, rivaroxaban, apixaban or edoxaban 4. Able to give informed consent for PPV and to participate in the trial	1. Patients unable to be operated under retrobulbar anaesthesia 2. Patients on antiplatelet therapy except if the antiaggregation is with acetylsalicylic acid 3. Patients who have recently started oral anticoagulation (less than 1 month before screening) 4. Any medical, psychological, psychiatric, geographic or social situation that could interfere with the participation of the patient in the trial or with the follow-up and adherence with the protocol and the evaluation of the results of the present trial

*PPV* pars plana vitrectomy

### Study randomisation

Upon completion of the screening assessment, participants who satisfy all the inclusion criteria and none of the exclusion criteria will be randomly assigned to the intervention and control groups in a 1:1 allocation ratio. Randomisation will be stratified by oral anticoagulation type: direct anticoagulation, which includes dabigatran, rivaroxaban, apixaban or edoxaban, and indirect anticoagulation, which includes acenocumarol. Randomisation assignment will be computer generated using the ‘randomizr’ library of the R statistical program R 3.4.0, with a complete randomising method based on permutations that guarantees balanced groups. The allocation sequence will be generated by the Methodology Unit of Navarrabiomed. Randomisation will be requested to the Clinical Trials Platform (CTP) of Navarrabiomed by the investigator responsible for patient recruitment. In return, CTP will send to this investigator an answer form by email that includes a randomisation number and the assigned treatment for this patient. Then, the investigator responsible for patient recruitment will give the information about treatment allocation to the anaesthetist, who will inform the patient. Throughout the study, the randomisation will be conducted by the CTP and the randomisation list will be kept by the CTP team for the duration of the study. Randomisation will be conducted without any influence of the investigators. The surgeons in charge, who will measure the outcomes, will be blinded. The data analyst will also be blinded, whereas participants and the rest of the investigators will not be blinded. Unblinding will not be allowed under any circumstance.

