### Statistics

#### Sample size

Considering that there is no difference in the probability of not having complications between the standard therapy (anticoagulant interruption) and the experimental therapy (no interruption of anticoagulant), and assuming a 95% confidence level and a 96% probability of not having complications, 48 patients are required in each arm (*n* = 48 × 2) in order to have an 80% probability that the upper limit of the confidence interval excludes a difference of over 10% in favour of the standard group. Calculations are performed by Sealed Envelope Ltd.

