#### Data analysis

A description of the sociodemographic and clinical characteristics of the patients involved in this trial will be performed for the complete sample and for each group using a mean with standard deviation or median with interquartile range for the quantitative variables, and using frequencies and percentages for the categorical variables. These characteristics will be compared between the control and experimental groups using parametric tests such as the Student *t* test and Chi-squared test, or nonparametric tests such as the Mann–Witney or Fisher tests. If any of the variables differs significantly between groups, this will be taken into account when comparing the outcomes. The incidence of haemorrhage (pre-, intra- and postoperative) and other categorical secondary variables, such as complications 3 months after surgery, both for the total sample and for each group, will be estimated by means of sample proportion with a 95% confidence interval and from baseline to 3 months after surgery will be compared between groups using parametric or nonparametric tests, such as the Student *t* test and Mann–Whitney test, depending on normality. If any sociodemographic or clinical characteristic differs between groups, lineal and logistic regression models will be used to compare the outcomes between groups, including them as covariates, which will provide adjusted odds ratios for the intervention, together with 95% confidence intervals. Sensitivity analyses will also be performed excluding patients with proliferative vitreoretinopathy or proliferative diabetic retinopathy, patients for whom scleral buckling procedures have been placed, and patients under treatment with acetylsalicylic acid to account for the possible bias induced after having included them. Additionally, a multivariate analysis including age and treatment with acetylsalicylic acid will also be performed to account for possible differences in the distribution of these variables among groups. SPSS software version 21.0 will be used to perform the analysis.

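### Randomisation is stratified by anticoagulant type, but no printed analysis uses the stratum; this makes the interval slightly too wide and does not bias it

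*Protocol article*

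**What the plan says.** The Study randomisation section of the protocol article says that patients are "randomly assigned to the intervention and control groups in a 1:1 allocation ratio" and that "Randomisation will be stratified by oral anticoagulation type". The direct stratum holds dabigatran, rivaroxaban, apixaban and edoxaban; the indirect stratum holds acenocumarol. The abstract and the opening of Methods and design also say that patients are stratified this way.

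The Data analysis section sets out:

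- group comparisons without covariates;
- a conditional rule: "If any sociodemographic or clinical characteristic differs between groups, lineal and logistic regression models will be used to compare the outcomes between groups";
- sensitivity analyses that leave out patients with proliferative disease, with scleral buckling or on acetylsalicylic acid;
- a further model: "a multivariate analysis including age and treatment with acetylsalicylic acid will also be performed".

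Anticoagulant type is named in none of them.

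The Study arms section makes the control regimen depend partly on the stratum. Every listed acenocumarol case receives enoxaparin. For direct agents, when glomerular filtration is above 50 ml/min and thrombotic risk is low, "anticoagulant treatment is suspended without the need for substitution treatment"; the other direct-agent cases receive enoxaparin.

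**The concern.** A factor used to stratify allocation is normally carried into the analysis, so that the standard error reflects the way patients were allocated. Here the article does more than stay silent. It names its covariates and fixes a rule for choosing others, and the rule selects on imbalance. Stratified allocation exists to prevent imbalance in this factor, so an analysis plan that followed the text would be expected to omit it.

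Two things are at stake. One is precision: an unstratified interval counts the between-stratum variation that the design has already removed. The other is the timing of the choice. With few events expected, adding the stratum after the data are seen would be a post hoc decision.

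**Working it through.** **Inputs from the Sample size section.** The plan is "assuming a 95% confidence level and a 96% probability of not having complications", an "80% probability that the upper limit of the confidence interval excludes a difference of over 10% in favour of the standard group", and "48 patients are required in each arm". The complication rate is therefore 4% in both arms and the margin is 10 percentage points.

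**Step 1: reproduce the plan's figure.** With unpooled variance,
n per arm = 2 × p(1−p) × (z₁₋α + z₀.₈)² / margin².
- One-sided 5%: 2 × 0.0384 × (1.645 + 0.842)² / 0.01 = 47.5, so 48. This matches the plan.
- One-sided 2.5%: 61, which does not match.

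The steps below use one-sided 5%, the level behind the stated 48. At 48 per arm, SE = √(2 × 0.0384 / 48) = 0.040, and power = Φ(0.10/0.040 − 1.645) = 80.4%.

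**Step 2: effect of using the stratum.** The article gives neither the split between strata nor stratum-specific rates, so both are assumed, with the overall rate held at 4%. The stratified variance is the sum over strata of share × p(1−p). The unstratified variance is 0.04 × 0.96 = 0.0384.

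| Share direct | Rates, direct / indirect | Stratified variance | Ratio | Unstratified SE too large by | Power if stratified | n per arm |
|---|---|---|---|---|---|---|
| 50% | 4% / 4% | 0.0384 | 1.000 | 0% | 80.4% | 48 |
| 50% | 2% / 6% | (0.0196 + 0.0564)/2 = 0.0380 | 0.990 | 0.5% | 80.7% | 47 |
| 50% | 1% / 7% | (0.0099 + 0.0651)/2 = 0.0375 | 0.977 | 1.2% | 81.2% | 47 |
| 50% | 0% / 8% | (0 + 0.0736)/2 = 0.0368 | 0.958 | 2.2% | 81.8% | 46 |
| 70% | 0% / 13.3% | 0.3 × 0.1333 × 0.8667 = 0.0347 | 0.903 | 5.3% | 83.8% | 43 |

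The sixth column is 1/√ratio − 1. The last row is the most extreme case tried. Stratifying never needs a larger sample.

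**Step 3: error rate at the margin.** The simulation used 200,000 trials per setting, 24 patients per arm per stratum, and simple Wald limits at one-sided 5%. False claims of non-inferiority were:
- control 4%, continuation 14% in both strata: 7.2% unstratified, 7.3% stratified;
- control 1%/7%, continuation 11%/17%: 7.3% and 7.5%.

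Omitting the stratum does not raise the error. The excess over 5% appears with either analysis and comes from Wald limits with few events, which is a reason to use a score-type or Newcombe interval.

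**Step 4: what results by stratum could show.** Expected events are 96 × 0.04 = 3.84 in total, or about two per stratum if the strata are equal. The chance that at least one stratum of 48 has no events is 1 − (1 − 0.96⁴⁸)² = 1 − (1 − 0.141)² = 26%. Two-sided 95% Newcombe intervals with 24 per arm:
- no events in either arm: the Wilson upper limit is 3.84/27.84 = 0.138, so about ±14 points;
- one event in each arm: the Wilson limits are 0.007 and 0.202 around 0.042, and √(0.035² + 0.160²) = 0.164, so about ±16 points.

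Both are wider than the 10-point margin.

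**The case against.** **This belongs in the statistical analysis plan.** The article condenses a fuller protocol, and the analysis plan is not shown. The sentence on comparing categorical outcomes also appears to have lost words, and the general statements that patients are stratified do not limit this to allocation. This stands in part: the claim can only be that none of the printed text uses the stratum. It does not remove the point, because the article names its covariates and fixes a selection rule that works against the stratification factor.

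**The effect is negligible and conservative.** This stands. Under the moderate assumed rates, power moves from 80.4% to at most 81.2%.

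**The pooled result mixes two different comparisons.** A reader might infer this from the Study arms section and expect estimates by stratum to separate two regimens. The document does not support that. Within each stratum the control regimen also depends on thrombotic risk and glomerular filtration rate, and enoxaparin 40 mg/24 h occurs in both strata. A direct-agent estimate would still combine controls with and without substitution. The primary objective is a single contrast, maintaining against interrupting therapy, and a pooled estimate addresses it.

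**Conclusion.** The point holds as a minor one. Randomisation is stratified by direct or indirect anticoagulant, no printed analysis uses that factor, and the imbalance rule would normally exclude it. The cost is a standard error about 0.5% to 1.2% too large under assumed stratum rates of 2%/6% to 1%/7% in equal strata. There is no cost if the rates are equal, and about 5% in the most extreme case tried. These sizes rest on an assumed split and assumed rates.

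A reader might go further and infer that the non-inferiority conclusion would be biased or invalid without the stratum. It would not: leaving the stratum out errs towards a wider interval and does not inflate the error. A reader might also expect results by stratum to show whether the treatment difference is similar in each. With about four expected events, they cannot.

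**What to change.** Before outcomes are known, state that:

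1. The primary risk difference and its confidence interval are stratified by anticoagulant type, for example with Mantel-Haenszel weights and a stratified Miettinen-Nurminen or Newcombe interval. The estimate remains calculable if one stratum has no events.
2. Anticoagulant type is a prespecified term in the visual acuity comparison and in any supportive regression model, whether or not it differs between arms. As printed, acuity is compared by t test or Mann–Whitney test, with regression only if characteristics differ, so the linear model would be fitted in any case. Any logistic model stays supportive: arm, stratum, age and acetylsalicylic acid make four terms for 3.84 expected events.
3. Event counts and risk differences by stratum, if shown, are descriptive. The text should say that so few events cannot show whether the difference is similar across strata, and that the strata do not isolate individual substitution regimens.

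The cost is a few sentences. The stratum is already recorded for every patient at randomisation, and no additional patients are needed.
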